##### rTMS Safety Considerations

Although the anticipated risks and adverse events of rTMS are mostly low or minimal, life support equipment will be made available near the laboratory. All study team members who operate the MagVenture machine will have standard training for procedures, including training in rTMS device operation, supervised repeated practice in rTMS procedures, and testing for interrater reliability in RMT determination.

The rTMS monitoring questionnaire administration, staff observation, and interactions with participants will occur daily. If immediate medical intervention is required, the participant will be referred to an appropriate medical facility; an ambulance may be called as needed. Information on all adverse events will be recorded and reported to the IRB with each continuing review application. Unexpected or serious adverse events will be promptly reported to the IRB. Standard seizure monitoring procedures will be in place [69], and video recordings will be collected during rTMS sessions to help evaluate the session as needed for training or a review of adverse events. In the event a participant reports an rTMS-related symptom (most often, headache), the physician on the protocol will be consulted. If deemed necessary by the physician, a single dose of acetaminophen will be administered.

### Statistical Analysis Plan

The statistical analysis will be conducted using Stata 18 (StataCorp LLC). All continuous measures will first be assessed for their distribution characteristics through the use of Shapiro-Wilk tests and the construction of histograms to determine whether assumptions are met for parametric analysis; if not, nonparametric alternatives will be used. Baseline clinical and demographic characteristics of participants will be assessed using descriptive statistical measures of central tendency and dispersion: means and SDs for those variables meeting assumptions for parametric analysis and medians, range, and IQRs for those not meeting assumptions. The primary outcome of changes in RRV (scores after rTMS−scores before rTMS) for both the active and sham conditions will be computed. Tests comparing the pre-post differences for the active and sham rTMS sessions will be conducted using 2-tailed paired *t* tests (if distributions are normal) or Wilcoxon signed rank tests if the assumptions of distribution are not met).

The EEG data, once collected, will be imported into the MATLAB platform (The MathWorks, Inc) for processing. Data will be filtered offline at 0.1 to 30 Hz and epoched (1000 ms before feedback to 2000 ms after feedback) to capture the FRN and RewP time windows and allow for time-frequency analyses (ie, reducing edge effects). Established preprocessing methods (eg, eye-blink correction, additional filtering, and bad-channel identification) will also be applied. Both theta (3-9 Hz) and delta (<3 Hz) power will be extracted and a principal component analysis applied. This data-driven approach helps separate meaningful segments of the time-frequency surface related to the FRN and RewP components. EEG data will be used to determine differences between active and sham rTMS on the neural modulation of reward [62,70,71]. Pearson and Spearman correlational coefficients will be used to evaluate the associations of clinical assessment measures with RRV and task-specific neural measures (eg, correlation between food craving scores and neural activation related to reward processing). We will control for any differences in hunger and fullness ratings before each RRV task in analyses examining changes in RRV.

We do not anticipate any period effects (ie, when the outcome of interest changes with time irrespective of treatment effect) because the condition of the treatment is stable for both active and sham rTMS. Regarding carryover effects, we anticipate that the effect of a single session of rTMS will last no more than 24 hours (the washout period is >5 times the anticipated duration of effects).

Regarding participant and rTMS operator ratings of active versus sham rTMS, we will report descriptive data on the percentage of participants and operators who correctly identified the active condition. Such reporting on the success of blind manipulation is standard in the rTMS field.

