### Design and Procedure Overview

A single-blind, within-participants, sham-controlled study is being conducted to perform an initial test of rTMS on the RRV of food, using a behavioral choice paradigm, and the neural modulation of reward, using an EEG (Figure 1).

Participants will attend 2 study visits that are separated by a washout period of at least 1 week (up to 4 weeks). Participants will receive active rTMS on 1 day and sham rTMS on the other day using a randomized and counterbalanced schedule. Participants will arrive at the laboratory fasted by 8 AM where they are asked to provide a urine sample for drug and pregnancy screening, complete an alcohol breath test, have their height and weight measured, and consume a standardized breakfast. During breakfast, participants will complete demographic, health history, and clinical behavioral and psychological questionnaires. After consuming breakfast, participants will complete a small sampling of 4 different palatable snack foods to determine which food will be used for the RRV measure for both study days. Participants will then complete the RRV measure and a reward task while an EEG is collected before rTMS (pre-rTMS EEG), receive rTMS, and complete the RRV measure and reward task again while an EEG is collected after rTMS (post-rTMS EEG). These procedures will allow for the comparison of pre- to posttest changes in the behavioral (RRV) and neural (EEG) modulations of reward between the active and sham rTMS conditions. Study procedures will be identical across study visits and conditions, except for certain baseline measures on the first day and the within-participant manipulation of active versus sham rTMS administration. A telephone follow-up to assess post-rTMS symptoms will be scheduled after the completion of each visit.

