### Primary and Secondary Outcome Measures

#### RRV of Food

The RRV of food will be measured by a validated behavioral choice questionnaire that asks participants to make a choice between receiving the food they rated as their most liked (ie, nacho cheese–flavored tortilla chips, original potato chips, candy bars, or chocolate chip cookies) and receiving money [60]. To determine how reinforcing food is in comparison with money, the behavioral choice questionnaire provides participants with 16 different choices, in which they make a choice between receiving the most liked food (100 kcal serving) and receiving the money (US $0.25). Each choice—food or money—is associated with a different number of button presses (using a tally clicker) required to gain access to the choice. Each of the 16 choices on the questionnaire requires the same number of button presses (ie, 20) for the money, whereas the number of button presses for the food increases with each choice. Choice 1 begins with 20 button presses for either the money or the food. The number of button presses required to receive the food increases in 20 response increments for choices 2 through 16. Thus, by choice 16, participants could have access to the food if they are willing to make 320 presses or receive the money for 20 presses. Participants will select whether they want money or food for choices 1 through 16. To produce valid responses, participants will be informed that they will be performing one of their choices by choosing 1 of 16 numbers from a hat, with the numbers representing the choice from the questionnaire (eg, if a participant randomly selects number 6, the participant will carry out the decision made for choice 6, which is either 120 button presses for the most liked food or 20 button presses for the money). After participants complete the number of button presses associated with the choice drawn, they will receive their choice (food or money). The reinforcing value of food is scored as the choice (1-16) when money is chosen instead of food. The higher the number associated with the choice of money, the higher the RRV of food. This measure has been shown to be valid and reliable for assessing the RRV of food [60].

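### The primary analysis subtracts the whole pre-rTMS score after the crossover pairing has already removed the person level; this costs precision unless the visit-to-visit differences in pre and post scores correlate at about 0.7 or more

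*Protocol article*

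**What the plan says.** The Statistical Analysis Plan section defines the primary outcome as "changes in RRV (scores after rTMS−scores before rTMS", computed for each of the two conditions. The comparison follows: "Tests comparing the pre-post differences for the active and sham rTMS sessions will be conducted using 2-tailed paired" t tests, with the Wilcoxon signed rank test as the alternative if the data are not normal. The Design and Procedure Overview describes the same contrast, a "comparison of pre- to posttest changes in the behavioral (RRV) and neural (EEG) modulations of reward between the active and sham rTMS conditions".

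The only adjustment named for this outcome concerns appetite: "We will control for any differences in hunger and fullness ratings before each RRV task in analyses examining changes in RRV". The pre-rTMS RRV score is not named as a covariate; it enters only by subtraction.

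The outcome is a bounded integer: "The reinforcing value of food is scored as the choice (1-16) when money is chosen instead of food". On measurement quality the RRV of Food section says "This measure has been shown to be valid and reliable for assessing the RRV of food [60" and gives no coefficient. The Sample Size and Power Considerations section plans for 10 analyzable participants, sets that number by pilot guidelines and practicality, and intends the observed effect size to feed the power calculation of a later trial.

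**The concern.** Change scores are usually chosen to take out stable differences between people. In this crossover the active-minus-sham contrast within each participant does that already. What the pre-rTMS score can still contribute is variation specific to a visit, such as a day on which a participant values food more than usual. If the pre and post scores share little of that variation, subtracting the pre score mostly adds its own variability to the result.

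Two things are at stake in a pilot of about 10 people. The confidence interval may be wider than it needs to be around an estimate that will size the next trial. A chance difference between a participant's two pre-rTMS scores also passes in full into that estimate.

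**Working it through.** **Inputs from the article.** Planned analyzable n = 10, from 12 enrolled (10 × 1.2 = 12; 10/12 = 83%). The test is two-sided and paired. Scores run from 1 to 16. Pre and post scores are taken on the same day, and visits are 1 to 4 weeks apart. No alpha, power, effect size, SD or correlation is stated, so there is no precision figure to reproduce.

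**Notation.** For each participant let DX and DY be the active-minus-sham differences in pre and in post RRV, with equal variance s² (assumed) and correlation r.

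**Variance of the estimated effect.**
- Change score, mean of DY − DX: 2s²(1 − r)/n.
- Regression of DY on DX, taking the intercept: s²(1 − r²)/n in large samples, times (n − 2)/(n − 3) for estimating the slope. At n=10 that factor is 8/7.
- Ratio, adjusted to change: (1 − r²)/[2(1 − r)] = (1 + r)/2 in large samples, and (1 + r)/2 × 8/7 at n=10.
- Break-even at n=10: (1 + r)/2 × 8/7 = 1 gives r = 0.75.

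**Results over a range of r.** Interval width and power are simulated (100,000 replicates, normal data, n=10). Power assumes a true effect of 0.8 SD of DY.

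| r | variance ratio, large n | variance ratio, n=10 | interval width ratio, n=10 | power, change | power, adjusted |
|---|---|---|---|---|---|
| 0 | 0.50 | 0.57 | 0.77 | 0.36 | 0.56 |
| 0.25 | 0.625 | 0.71 | 0.86 | 0.46 | 0.58 |
| 0.5 | 0.75 | 0.86 | 0.94 | 0.62 | 0.68 |
| 0.75 | 0.875 | 1.00 | 1.01 | 0.89 | 0.88 |
| 0.9 | 0.95 | 1.09 | 1.05 | 0.999 | 0.995 |

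Type I error, checked at r=0.25, was 0.05 for both methods. With a visit term added to the adjusted model, power was 0.65 against 0.62 for the change score at r=0.5, 0.72 against 0.71 at r=0.6, and 0.79 against 0.80 at r=0.68. The gain therefore runs out sooner.

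**On the 1 to 16 integer scale.** Assumptions: mean 8.5, person SD 4, error SD 1.5, effect −2 points, n=10, no visit term. Power for change against adjusted was 0.42 and 0.60 (r=0.10), 0.42 and 0.53 (r=0.29), 0.42 and 0.47 (r=0.48), 0.41 and 0.43 (r=0.62), 0.39 and 0.38 (r=0.77). With a mean of 13, nearer the ceiling, the gain at r of about 0.46 was only 0.39 to 0.42. With a visit term the gain vanished near r=0.62 at a mean of 9, and near 0.5 at a mean of 13.

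**Chance imbalance.** Given an observed mean DX, the change-score estimate is expected to miss by (r − 1) × mean DX. If the active-day pre score is 1 point higher by chance, that is −0.75 points at r=0.25 and −0.25 points at r=0.75. Over randomized orders the error averages to zero.

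**How r relates to familiar correlations.** r = (within-visit pre/post correlation − cross-visit pre/post correlation)/(1 − between-visit correlation). With the last two at 0.7, a within-visit correlation of 0.8 gives (0.8 − 0.7)/(1 − 0.7) = 0.33. With the last two at 0.6, a within-visit correlation of 0.9 gives (0.9 − 0.6)/(1 − 0.6) = 0.75. A raw pre/post correlation does not fix r. If it is 0.87, error is 0.13 of the variance and r = v/(v + 0.13), where v, the visit share, can lie anywhere from 0 to 0.87. So r can lie anywhere from 0 to 0.87.

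**The case against.** The strongest reply is that everything turns on r, and the article does not give it. A reader might infer that r must be low because the baseline is noisy. The documents do not support that: they call the measure reliable and give no coefficient. Same-day pre and post scores on the same food, with visits weeks apart, could share real day-to-day variation and push r up. The standardized fast and breakfast and the identical procedures reduce such variation. The snack and the payout of the drawn choice between the two measurements may weaken the link. These arguments pull both ways and do not settle r. The objection stands, so the loss can only be stated conditionally.

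A reader might also infer that the change score biases the result. It does not. Under randomized order it is valid, targets the same effect as the adjusted estimate, and matches the stated objective of comparing pre-to-post changes. There is also no power target to miss, because the sample size rests on pilot guidelines.

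Two practical objections stand in part. With 10 participants, one extreme pre-score difference has leverage on the regression. The plan's Wilcoxon fallback would also be lost if the regression simply replaced the current test. Both argue for keeping the change-score test as a sensitivity analysis, not for leaving it as the only analysis.

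**Conclusion.** The point holds as a conditional loss of precision. At n=10, and with equal pre and post variances, baseline adjustment would cut the variance by about 43% at r=0, 29% at r=0.25 and 14% at r=0.5. It breaks even at r=0.75 and costs about 9% at r=0.9. On power, the advantage ends at an r of about 0.5 to 0.7, sooner when scores sit near the ceiling or a visit term is included. All of these r values are assumptions.

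The potential gain at low r is much larger than the potential loss at high r, and the pre-rTMS scores are collected anyway. The promise to control for hunger and fullness cannot be met by a plain paired t or Wilcoxon test, so some model is needed in any case. The change is worth making; leaving it undone would not invalidate the result.

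**What to change.** Prespecify as the primary analysis a regression of each participant's active-minus-sham difference in post-rTMS RRV on the active-minus-sham difference in pre-rTMS RRV, with the intercept as the treatment effect and its confidence interval. Keep the change-score paired t or Wilcoxon test as a sensitivity analysis, which also covers non-normal data. Report the pre/post and between-visit correlations so that the next trial can choose its analysis on evidence.

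The change is to wording only, with no new data. It spends one degree of freedom, loses slightly if r exceeds about 0.7, and needs a check for influential pre-score differences. Each further covariate (visit, hunger, fullness) costs another degree of freedom, so state in advance which of them enter the primary model and which are left to sensitivity analyses.

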After completing the questionnaires, participants will be asked to sample 4 different palatable snack foods (ie, Doritos nacho cheese–flavored tortilla chips [Frito Lay], Lay’s original potato chips [Frito Lay], Twix candy bars [Mars, Incorporated], and Chips Ahoy chocolate chip cookies [Mondelez International]) and rank their liking of each on a 100-mm visual analog scale anchored by *dislike very much* and *like very much* at either end. The food that participants rate as their most liked will be used for the RRV measure [60] at both study visits. After food sampling, participants will indicate their current levels of hunger and fullness using visual analog scales before being prepared for EEG procedures and completing the RRV measures and another reward task during the EEG procedure. Participants will consume a snack before undergoing rTMS to limit the potential effects of physiological hunger. After rTMS, they will complete the RRV and reward measures while an EEG is collected (RRV and reward measures as well as EEG and rTMS procedures are described in the following subsections). Participants will then be debriefed and monitored for any side effects, scheduled for their second study visit, compensated for their time, and discharged. After the washout period, participants return to the research center for their second visit. The washout period, identical testing procedures and environments, and counterbalancing procedures are intended to cancel out any carryover effects within the active and sham rTMS conditions. Procedures completed during the first study visit will be extended to the second study visit with the exception of randomization, height measurement, food sampling, and the completion of questionnaires used to determine study eligibility (ie, Patient Health Questionnaire-9, Wide Range Achievement Test-4, Adult ADHD Self-Report Scale, and Edinburgh Handedness Inventory). At the end of study visit 2, a brief rTMS blind assessment will be performed where the participant will be asked whether the rTMS session that day was active or sham. The participant will be asked to rate how confident they are in their choice on a scale ranging from 0 (*not at all confident*) to 10 (*very confident*).

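### Period effects are dismissed for a reason that does not address visit differences, so the primary paired test has no visit term although snack tasting precedes the first RRV measurement at visit 1 only

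*Protocol article*

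**What the plan says.** All references are to the Protocol article.

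- **Design and Procedure Overview:** "Participants will receive active rTMS on 1 day and sham rTMS on the other day using a randomized and counterbalanced schedule".
- **Statistical Analysis Plan, outcome and test:** "The primary outcome of changes in RRV (scores after rTMS−scores before rTMS") is computed for each condition. Then: "Tests comparing the pre-post differences for the active and sham rTMS sessions will be conducted using 2-tailed paired" t tests, or Wilcoxon signed rank tests if normality fails. Neither test has a term for visit or sequence. The section also promises control for differences in hunger and fullness ratings before each RRV task.
- **Statistical Analysis Plan, period effects:** "We do not anticipate any period effects (ie, when the outcome of interest changes with time irrespective of treatment effect"), and the reason given is "because the condition of the treatment is stable for both active and sham rTMS".
- **Study Visits:** at visit 1 participants taste four snack foods before the first RRV: "After food sampling, participants will indicate their current levels of hunger and fullness using visual analog scales before being prepared for EEG procedures". Visit 2 repeats visit 1 "with the exception of randomization, height measurement, food sampling, and the completion of questionnaires used to determine study eligibility".
- **Results:** of 17 enrolled, 3 were lost before rTMS, 5 withdrew after rTMS, 4 were in progress and 5 had completed. The sequences of those lost are not given.

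**The concern.** The protocol defines a period effect as change over time irrespective of treatment. A stable treatment condition cannot rule that out, because period effects come from the participant, the task and the visit. The statement is nevertheless the only support offered for a primary test that ignores visit.

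The visits also differ at a point close to the outcome. The Study Visits section says the standardized breakfast and snack are there to lessen the influence of hunger and of the palatability of foods eaten on the RRV. Tasting four palatable snacks then comes before one of the four RRV measurements and no other.

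If the change in RRV differs by visit, two things are at stake. With balanced sequences, the period effect enters the paired differences as extra variance. With unbalanced sequences, part of it enters the treatment estimate. The Sample Size and Power Considerations section uses the observed effect size to plan the next trial, so either distortion would carry forward.

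**Working it through.** **Figures in the plan.** The protocol states no effect size, SD, alpha or power, so there is no power figure to reproduce. Planned enrolment follows as 10 × 1.20 = 12 (10/0.80 would give 12.5), and 10/12 = 83%. Loss to date is (3 + 5)/17 = 8/17 = 47%, against the 20% assumed. The 17 enrolled can yield at most 17 − 8 = 9 completers.

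**Model.** For each completer let D = (RRV change under active) − (RRV change under sham). Then

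D = τ + s·π + e,

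where τ is the treatment effect and π is the visit 2 minus visit 1 difference in the RRV *change*. The sign s is +1 if active is at visit 2 and −1 if it is at visit 1, and SD(e) = 1. Because D is built from within-visit changes, a shift common to the pre and post scores of a visit cancels. Only an unequal shift contributes to π.

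**Bias of the paired mean, given the split.**

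Bias = π × (n active second − n active first)/n.

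- 5:5: 0.
- 7:3: π × 4/10, so 0.20 SD in size at π = 0.5 and 0.40 SD at π = 1.
- 6:3: π × 3/9, so 0.17 SD and 0.33 SD.

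The average of the two sequence means has zero bias at every split.

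**Size and power.** These come from simulation with at least 100,000 runs per setting, two-sided alpha 0.05. The assumed true effect is 1 SD, which gives the paired test about 80% power at n = 10. The adjusted test is the two-sequence t test on n − 2 degrees of freedom. The values of π are assumptions, since the documents give none. Results at 5:5:

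| π (SD) | Type I error, paired | Power, paired | Power, adjusted |
|---|---|---|---|
| 0 | 5.0% | 80% | 79% |
| 0.25 | 4.4% | 78% | 79% |
| 0.5 | 2.9% | 72% | 79% |
| 1 | 0.7% | 48% | 79% |

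The standardised effect shrinks for the same reason. At 5:5 the expected variance of D is 1 + π²·n/(n − 1). At π = 0.5 this is 1 + 0.25 × 10/9 = 1.278, so the SD is 1.13 and the effect size is multiplied by 1/1.13 = 0.88, about 12% smaller.

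At 7:3 and π = 0.5 the paired test has type I error of about 6%, against 5% adjusted. With no period effect at 7:3, power is 80% paired and 72% adjusted.

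**How likely is imbalance?** Both cases assume that losses are unrelated to sequence.

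- If 9:8 were enrolled and 9 complete, the sequence counts differ by 3 or more with probability 0.35.
- If 7:7 were treated and 9 complete, the probability is 0.27.

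Nine is an odd number, so exact balance is impossible at that count. Further enrolment could restore it.

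**The case against.** The strongest reply is that no period effect has been shown. The outcome is a within-visit change, the tasting is small, and hunger ratings and EEG preparation come between it and the first RRV. Both visits have the same standardized breakfast and snack, and hunger and fullness are to be controlled. This stands as far as it goes: a reader might infer that the protocol builds in a period effect, and the documents do not support that. They do not exclude one either. Tasting directly precedes the pre-rTMS block, while a snack and rTMS come before the post score. Adjustment for hunger and fullness need not capture a response to palatability.

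A reader might also infer that withdrawals have already broken the counterbalancing. The sequences of those lost are not reported, so this is a risk and not a fact. If losses are unrelated to sequence, the paired estimate is unbiased on average over randomizations, and at π = 0.5 the type I error averaged over the likely splits is about 4%, below nominal. A clearly inflated error of about 8.6% needs a 7:2 split, and a split that extreme or worse has probability of about 5.7% from 9:8 enrolled.

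Finally, the Study Visits statement that "counterbalancing procedures are intended to cancel out any carryover effects within the active and sham rTMS conditions" might be read as leaving carryover unprotected. The same sentence also names the washout and identical procedures, and the Statistical Analysis Plan relies on an effect of at most 24 hours against a washout of at least 1 week. Carryover is no part of this point.

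**Conclusion.** The point holds in a limited form. The reason for expecting no period effects does not bear on the protocol's own definition of them, and the primary test omits visit although the visits differ just before the first RRV.

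The size depends on an unknown π. The loss at 5:5 is negligible at 0.25 SD, about 7 points of power at 0.5 SD and about 31 points at 1 SD, each against the adjusted analysis. The bias at 7:3 and 0.5 SD is 0.2 SD, conditional on that split. These figures assume normal errors and a period effect common to all participants.

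For a pilot with randomized order this is a cheap improvement that should be made. It does not show that the planned test is invalid.

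**What to change.** Before the data are analysed:

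1. Make the primary analysis a model of RRV change with condition and visit as fixed effects and participant as random effect. Keep the hunger and fullness control already promised, which a plain paired t or Wilcoxon test cannot carry. Without those covariates, for completers, this is the comparison of the two sequences.
2. Report the number of completers in each sequence.
3. Delete the statement that period effects are not anticipated.
4. Leave the visit 2 tasting as it is. Five participants have completed, and a change now would make the visit difference vary between participants, which a single visit term could not absorb.

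The cost is a change of wording and one residual degree of freedom. With no period effect and a true effect of 1 SD, power goes from 80% to 79% at 5:5. If completers end at 7:3 the price is higher, 80% to 72%, and the sponsor should accept that trade-off knowingly.
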